**Figure 1 F1:**
[figure not shown]
Trial design.

Box 1Eligibility criteriaInclusion criteriaAdult patient (≥18 years)New referral (defined as being referred within the last 6 weeks) to a public hospital physiotherapy outpatient clinic with a musculoskeletal condition or musculoskeletal pain (hereafter referred to as ‘musculoskeletal pain’) that would usually be managed by a physiotherapist. Examples include but are not limited to:Back/neck painOsteoarthritisWhiplash-associated disordersAnkle sprainsPostfractureSporting injury (eg, ankle sprains)Postorthopaedic surgery (eg, hip or knee replacement, rotator cuff repair)Willing to participate and provide follow-up dataCan speak and read English to provide informed consentExclusion criteriaSuspected serious underlying pathology or musculoskeletal conditions requiring urgent medical care (eg, malignancy, fracture, infection, inflammatory arthritis and joint dislocation)New referral strongly suggestive of concerning neurological features (eg, progressive radiculopathy or upper motor neuron lesion)Is on a postoperative exercise regimen prescribed by a surgeon which specifies the mode of care delivery (eg, needs to be provided in a clinic supervised by a physiotherapist)Requiring mobility progression or assistance weaning from a walking aid(s) whereby the person is at an increased fall risk and needs to be seen in the clinicPregnant women.

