### Randomisation procedure

The 1:1 random allocation sequence will be independently generated in Stata by the team’s biostatistician and uploaded to REDCap. Allocation will be concealed as the biostatistician generating the sequence will not be involved in the recruitment of participants and the screening physiotherapist will not know the participant’s group allocation until their baseline data are entered into REDCap. The allocation sequence will also be concealed from potential participants and all on-site staff associated with the trial. The randomisation sequence will use randomly permuted blocks of variable sizes (2 and 4) to ensure equal numbers in both groups. Stratification variables for the randomisation sequence include trial sites and the three treatment subgroups. This will ensure that the intervention and control groups have a similar proportion of participants across different trial sites. The screening physiotherapist will telephone participants who consent (via completing the PCF—online supplemental appendix 2) and complete their baseline assessment to inform them of their group allocation. Table 1 describes the physiotherapist-led triage and treatment service and usual care group.

**Table 1 T1:** Physiotherapist-led triage and treatment service and usual care protocol.

Treatment group and subgroup	Intervention protocol
Physiotherapist-led triage and treatment service	
*All participants*	For participants randomised to the physiotherapist-led triage and treatment service, the screening physiotherapist will match them to different modes and types of care during the call informing participants of their group allocation.
*Low risk* of poor outcomes	Participants at low risk of poor outcomes (Keele STarT MSK tool score 0–4)^28^ will be offered brief advice and education (via one telephone call with a physiotherapist) including advice on activity modification, analgesia if necessary and education that their condition has a good prognosis. This advice and education will be provided during the phone call where participants are informed of their trial arm allocation. Participants in this treatment subgroup will be asked to call the screening physiotherapist back if their symptoms have not improved in 6 weeks. If nil contact is received after 6 weeks, participants will be discharged from the physiotherapy service.

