*Medium risk* of poor outcomes or requiring postoperative rehabilitation	Participants at medium risk of poor outcomes (Keele STarT MSK tool score 5–8) or requiring postoperative rehabilitation will be offered physiotherapy via telehealth. An appointment with a telehealth physiotherapist will be organised by the screening physiotherapist during the phone call where participants are informed of their trial arm allocation. Telehealth physiotherapy will consist of assessment, advice, education to support self-management and a tailored home-exercise programme delivered via the PhysioTherapy Exercise App (freely available online exercise prescribing software created by some of the study authors: www.physiotherapyexercises.com). The number of appointments offered will be at the discretion of the treating physiotherapist.
*High risk* of poor outcomes and/or with potential nonprogressive radiculopathy	Participants at high risk of poor outcomes (Keele STarT MSK tool score 9–12) and/or with potential nonprogressive radiculopathy will be offered a course of clinic-based (in-person) physiotherapy as is usually provided at the participating public hospital clinics. An appointment with a clinic-based physiotherapist will be organised by the screening physiotherapist during the phone call where participants are informed of their trial arm allocation. Participants will be offered clinic-based care but will not be told they are at high risk of poor outcomes (according to the Keele STarT MSK tool). Clinic-based physiotherapy may include a combination of any advice and education to support self-management (eg, advice to exercise, modify activities, lose weight or take simple pain medications if needed), exercise tailored to patients’ activity goals and level of function, graded activity, graded exposure and manual therapy. The number of appointments offered will be at the discretion of the treating physiotherapist.
Usual care	

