### Primary analysis

The purpose of our trial is to assess whether the physiotherapist-led triage and treatment service is as good as or better than usual clinic-based care for improving function and better than usual care in terms of reducing treatment waiting time. The between-arm difference in PSFS scores at 6 months postrandomisation is a coprimary outcome and we have prospectively defined a noninferiority margin of −0.7 points for this analysis. This is the maximal compromise on the outcome we are prepared to tolerate (based on guidelines^18^ and consumer feedback) and still consider the physiotherapist-led triage and treatment service to be clinically noninferior to usual clinic-based care. We will test the null hypothesis that the mean difference in PSFS scores (intervention − usual care) is no greater than −0.7 (H0: mean difference ≤−0.7). To declare noninferiority for the new model of care when compared with usual clinic-based care, the 95% CI around the mean difference should be entirely above the noninferiority margin, that is, the lower bound of the 95% CI must be higher than −0.7. A repeated-measure linear mixed model including all postrandomisation PSFS measurements will be used to generate an adjusted mean difference and 95% CI representing the comparison of PSFS scores between the intervention and usual care arms at each time point. The model will be adjusted for the baseline PSFS value (to improve statistical precision), hospital site and treatment subgroup allocation.

The between-arm difference in treatment waiting time is the other coprimary outcome, provided the physiotherapist-led triage and treatment service is as good or better than usual clinic-based care for improving function (hierarchical approach). We have prospectively defined an effect size of 14 days or greater to be clinically important (approximately half the reduction found in the PhysioDirect trial).^8^ This is the difference that our consumers and clinician partners consider meaningful. A generalised linear model will be used to generate an adjusted mean difference and 95% CI representing the comparison of treatment waiting times between the intervention and usual care groups. The model will be adjusted for hospital site and treatment subgroup allocation.

Imputation techniques may be considered if more than 5% of any outcome data are missing, depending on patterns within missing data.

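### Postoperative and medium-risk patients share one stratum and one covariate level; adjusting separately for surgery and the STarT MSK score would recover a little precision, but nothing is biased

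*Protocol article*

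**What the plan says.** Box 1 admits surgical patients ("Postorthopaedic surgery (eg, hip or knee replacement, rotator cuff repair" and similar) alongside people with back pain, neck pain or osteoarthritis. Table 1 then sorts everyone into three treatment subgroups. The middle one reads: "Participants at medium risk of poor outcomes (Keele STarT MSK tool score 5–8) or requiring postoperative rehabilitation will be offered physiotherapy via telehealth". A postoperative patient can therefore enter this level without scoring 5–8.

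The Randomisation procedure section uses the same grouping: "Stratification variables for the randomisation sequence include trial sites and the three treatment subgroups". The Primary analysis section carries it into both coprimary models. For function: "The model will be adjusted for the baseline PSFS value (to improve statistical precision), hospital site and treatment subgroup allocation". For waiting time: "The model will be adjusted for hospital site and treatment subgroup allocation". Neither list contains surgery status or the STarT MSK score as a term of its own.

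Both items should be available before allocation. The section on randomisation states that "the screening physiotherapist will not know the participant’s group allocation until their baseline data are entered into REDCap", and the subgroup has to be known in order to stratify on it. Surgery also comes up at screening, since one exclusion criterion is "Is on a postoperative exercise regimen prescribed by a surgeon which specifies the mode of care delivery".

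**The concern.** The treatment subgroup records which pathway the intervention arm would offer. It is not a measure of prognosis. Its middle level puts two kinds of patient together, and for the postoperative ones the risk score no longer shows. If the two kinds differ in 6-month PSFS after allowing for baseline PSFS, site and subgroup, that difference stays in the residual variance of the function model.

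The function comparison is judged against a margin of 0.7 points, and waiting time is interpreted only if non-inferiority is shown. Precision on PSFS therefore matters for both coprimary outcomes. The plan adjusts for baseline PSFS explicitly to gain precision, and the same reasoning extends to other prognostic items already in hand.

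**Working it through.** **Inputs from the article (Sample size).** 368 participants, 184 per arm; margin 0.7; SD 1.9; two-sided α of 5%; 15% loss to follow-up; waiting-time difference 14 days with SD 43.

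**The plan's own figures.**
- PSFS: n per arm = 2 × 1.9² × (1.960 + 1.282)² / 0.7² = 154.8, so 155. Dividing by 0.85 gives 183 per arm, 366 in total. The noncentral-t version gives 156, then 184 per arm, which is the stated 368.
- PSFS power at 184 × 0.85 = 156.4 evaluable per arm: SE = 1.9 × √(2/156.4) = 0.2149; 0.7/0.2149 − 1.960 = 1.298; power 90.3%.
- Waiting time: SE = 43 × √(2/156.4) = 4.86; 14/4.86 − 1.960 = 0.919; power 82.1%, in line with the stated figure of more than 80%.

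The sample size reproduces, and the merging does not alter it.

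**Assumptions, because the article gives no figures.** Surgical share of the trial p = 20–40%; merged level's share s = 50–60%; 6-month PSFS gap d = 0.5–1.5 points between surgical and other patients in the merged level after the planned adjustment. All surgical patients are taken to fall in the merged level. The SD of 1.9 is treated as the residual SD of the planned model.

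**Variance a surgery indicator could remove.** The merged level is already in the model, so only variation inside it is left. With q = p/s as the surgical share within that level:

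R² = s × q × (1 − q) × d² / 1.9²

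Power is then recomputed with SD = 1.9 × √(1 − R²).

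| p | d | s | q | s·q(1−q) | R² | Power |
|---|---|---|---|---|---|---|
| 0.2 | 0.5 | 0.5 | 0.40 | 0.120 | 0.008 | 90.5% |
| 0.2 | 0.5 | 0.6 | 0.33 | 0.133 | 0.009 | 90.5% |
| 0.3 | 1.0 | 0.5 | 0.60 | 0.120 | 0.033 | 91.2% |
| 0.3 | 1.0 | 0.6 | 0.50 | 0.150 | 0.042 | 91.4% |
| 0.4 | 1.5 | 0.5 | 0.80 | 0.080 | 0.050 | 91.7% |
| 0.4 | 1.5 | 0.6 | 0.67 | 0.133 | 0.083 | 92.5% |

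These rows pair a larger share with a larger gap. Crossing p = 0.2, 0.3 and 0.4 with every d and s widens the range slightly, to R² of 0.006–0.093 and power of 90.4–92.8%.

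**Chance imbalance.** The SD of the between-arm difference in surgical share is √(4 × s × q(1−q) / N), with N = 2 × 156.4 = 312.8. For the tabulated values it is 3.2 to 4.4 percentage points. A 10-point imbalance is thus 2.3 to 3.1 SDs out, with two-sided probability of about 0.2–2%. With d = 1 it would move the estimate by 0.10 × 1 = 0.10 points, or 14% of the margin.

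**Type I error.** A simulation of 20,000 trials at the margin used a case more extreme than any above (s = 0.6, q = 0.5, d = 2). The one-sided error was 0.0254 without the surgery covariate and 0.0245 with it, against a nominal 0.025. The simulation standard error is √(0.025 × 0.975 / 20,000) ≈ 0.001, so neither departs from nominal.

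**The case against.** The strongest reply is that nothing here is an error. The plan stratifies by site and subgroup and adjusts for the same factors, which is standard practice. Grouping by pathway is defensible because the pathway determines what the intervention arm receives. Extra covariates are often left to the analysis plan, which the article promises before unblinding and which is not shown. The trial already reaches its stated 90% power. All of this stands, and it is why the point is an optional improvement. What remains is that the article does list the covariates for each coprimary model, and the list can be improved at almost no cost.

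A reader might infer more than the text supports:

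- **That surgical case mix is left uncontrolled.** Randomisation balances it in expectation within each site-by-subgroup stratum; only forced balance is missing. Baseline PSFS may also absorb part of any difference in the function model.
- **That a chance imbalance threatens the conclusion separately from the power loss.** The confidence interval already allows for chance imbalance, so these are one effect. A 10-point imbalance is also a tail event.
- **That the indicator could explain up to 15% of residual variance and lift power to 94%.** Those values come from p(1 − p)d²/1.9² at p = 0.4 and d = 1.5, which ignores that the merged level is already in the model.
- **That surgical patients recover along a different course.** The article does not say so. The gap d is an assumption.
- **That precision is shown to be lost on waiting time.** Nothing in the article indicates how strongly surgery predicts waiting time. Nor has any gain been quantified for the continuous score, which partly duplicates the subgroup term built from it.

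**Conclusion.** The point holds as a small, nearly free gain in precision. Surgery status and the STarT MSK score are folded into a three-level pathway factor, and neither is adjusted for separately in the stated models. There is no bias and no type I error inflation, and the sample size stands. On the stated assumptions a surgery indicator would explain about 1–8% of residual PSFS variance and raise power from 90.3% to about 90.5–92.5%, a gain of roughly 0.2 to 2 percentage points. The result depends entirely on the assumed surgical share, merged-level share and outcome gap; with no gap there is no gain.

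A neighbouring matter bears on the assumption that all surgical patients sit in the merged level. Table 1 gives no precedence when a postoperative patient scores 0–4, or also meets the third definition, "Participants at high risk of poor outcomes (Keele STarT MSK tool score 9–12) and/or with potential nonprogressive radiculopathy". Such a patient fits two subgroups, so those definitions need to be reconciled. That is a separate point and does not change the size given here.

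**What to change.** In the Primary analysis section, or in the statistical analysis plan before unblinding, prespecify:

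1. a postoperative (yes/no) covariate in the PSFS model and, for consistency, in the waiting-time model;
2. the baseline STarT MSK score (0–12) as a continuous covariate in the PSFS model, provided it is recorded for postoperative patients as well. The article does not say so outright, so the trial team should confirm it.

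Keep baseline PSFS (in the function model), site and treatment subgroup as covariates, and leave the randomisation strata unchanged. A fourth subgroup level would raise the site-by-subgroup cells from 6 × 3 = 18 to 6 × 4 = 24, about 15 participants per cell instead of 20, and is not needed for this gain.

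The cost is a sentence or two of analysis wording, about two degrees of freedom in the PSFS model, and some overlap between the score and the subgroup term. No new data are needed if the score is held for everyone. Fixing the terms now also avoids a dispute over post hoc adjustment if surgical case mix happens to differ between the arms.

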### Outcomes

The coprimary outcomes are physical function as assessed by the Patient Specific Functional Scale (PSFS) at 6 months postrandomisation and treatment waiting time (from randomisation to first treatment). PSFS scores at 3 and 12 months are secondary outcomes. Participants completing the PSFS list up to five functional tasks currently limited by their musculoskeletal condition and score each task based on their current level of ability—0 (unable to perform activity) to 10 (able to perform activity at the same level as before the complaint). Scores for each activity will be summed and calculated as an average of the total possible score for the participants (determined by the number of identified activities). This generic measure will be used as patients with a wide range of musculoskeletal pain presentations will be included in the trial, and it compares well with disease-specific measures in terms of reliability and validity.^10 12 13^ Treatment waiting time will be assessed as the number of days from randomisation to the first appointment with a physiotherapist (either telephone, video conference or clinic-based). It will also be expressed as the number of days from the referral date to the first appointment with a physiotherapist to understand treatment waiting times across sites before, during and at the end of the trial recruitment period; this will be a secondary outcome.

Secondary outcomes (eg, pain and quality of life), health resource measures (eg, number of clinic-based appointments and number of telehealth appointments), potential mediators (eg, pain self-efficacy and recovery expectations), process measures (eg, adherence and usability of PT eXercises App) and adverse events are outlined in online supplemental appendix 3.

### Data collection methods

Participants will receive a unique link via email or SMS to complete their surveys directly in REDCap. Participants will receive an email or SMS 2 days prior to each time point, reminding them to complete their respective surveys. Two reminders followed by a phone call will be provided to patients who do not complete their surveys at a particular time point. The treating clinicians may remind participants to complete their surveys during appointments. If requested, paper copies of the surveys will be posted (including a pen and a postage-paid return envelope) to participants with their responses entered directly into REDCap by an assessor blind to group allocation. If required, a study investigator may contact participants to assist them in completing their surveys, so they can post their survey responses to the screening physiotherapist via a postage-paid return envelope.

### Sample size

A total sample of 368 participants will provide 90% power to exclude a noninferiority margin of 0.7 points on the 11-point PSFS with a 15% loss to follow-up,^8^ an SD of 1.9, two-sided α of 5% and PSFS at 6 months in the control arm participants of 5.8—based on a recent trial conducted in the same setting.^14^ A between-group difference of ≤0.7 points will indicate that the new physiotherapy model of care is noninferior (as good as or better) compared with usual clinic-based care. We chose an SD of 1.9 as it is between the mean value of the SD for the PSFS at follow-up in published studies of similar patient populations with the SDs of 1.7,^15^ 2.0^12^ and 2.1^16^. The minimal important difference (MID) for the PSFS ranges from 1.3 (small change) to 2.7 (large change).^17^ Guidelines suggest using a noninferiority margin of 50% (or less preferably) of the expected treatment effect.^18^ Thus, we chose a conservative between-group noninferior margin of 0.7 (50% of the MID of 1.3).

If our physiotherapist-led triage and treatment service is noninferior for improving function at 6 months compared with usual care, we will interpret the findings for treatment waiting time as a coprimary outcome. This hierarchical approach to our coprimary outcomes was selected because consumer feedback suggested that reducing waiting times is not valuable if patient outcomes are adversely affected. Our sample size of 368 participants will provide >80% power to determine a conservative 14-day mean reduction in waiting time (approximately half of the reduction found in the PhysioDirect trial^8^), calculated from medians and interquartile ranges with this formula,^19^ using an SD of 43 (conservative SD from participating public hospital outpatient clinics over the past 5 years), two-sided α of 5% and 15% loss to follow-up.

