**Methods and analysis:**

A total of 368 participants (184 per arm) will be recruited from six public hospitals located in metropolitan Sydney, Australia. We will recruit adult patients newly referred to a public hospital physiotherapy outpatient clinic with a musculoskeletal condition that is typically managed by a physiotherapist (eg, back or neck pain, osteoarthritis, rehabilitation postorthopaedic surgery and sporting injuries). Participants will be randomised 1:1 to the physiotherapist-led triage and treatment service or usual care. A physiotherapist will telephone participants in the intervention group and match them to different modes and types of care based on baseline characteristics. Participants at low risk of poor outcomes (assessed by the Keele STarT MSK tool) will be given simple advice and education during this call and instructed to call back if their symptoms do not improve in 6 weeks. Participants at medium risk of poor outcomes or requiring postoperative rehabilitation will be offered a course of telehealth (videoconference) physiotherapy targeting exercise-based self-management. Participants at high risk of poor outcomes and/or with potential nonprogressive radiculopathy will be offered a course of usual clinic-based physiotherapy as per all participants in the usual care group. Physical function (Patient Specific Functional Scale) at 6 months postrandomisation and waiting time (time from randomisation to first treatment) are coprimary outcomes. Secondary outcomes include other patient outcomes (eg, pain), health resource use, adverse events, process measures (eg, adherence) and costs.

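### The stated power of over 80% for waiting time belongs to that test alone; the probability of concluding both noninferiority and a shorter wait is about 74% on the protocol's own inputs

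*Protocol article*

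**What the plan says.** The aim has two parts: noninferior function at 6 months and a shorter wait for treatment (Introduction and Primary analysis).

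The Sample size section powers the first part with 368 participants: "90% power to exclude a noninferiority margin of 0.7 points on the 11-point PSFS with a 15% loss to follow-up", with an SD of 1.9 and a two-sided α of 5%. The decision rule under Primary analysis is that "the lower bound of the 95% CI must be higher than −0.7".

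The second part depends on the first: "If our physiotherapist-led triage and treatment service is noninferior for improving function at 6 months compared with usual care, we will interpret the findings" for waiting time as a coprimary outcome. Primary analysis repeats this condition and calls the approach hierarchical.

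In the same paragraph as the condition comes the power statement: "Our sample size of 368 participants will provide >80% power to determine a conservative 14-day mean reduction in waiting time". Its inputs are given as "using an SD of 43 (conservative SD from participating public hospital outpatient clinics over the past 5 years") and "two-sided α of 5% and 15% loss to follow-up". No joint power is given.

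**The concern.** In a fixed sequence the second test keeps its full α, and the price is paid in power: the second claim can be made only if the first test also succeeds. None of the inputs listed for the waiting-time power (14 days, SD 43, α, loss) reflects the chance of stopping at the first step. A reader who sees the hierarchy and then a power above 80% may take that as the chance that the trial can claim shorter waits if its assumptions hold.

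The joint result matters most by the protocol's own reasoning. The hierarchy was chosen because consumers saw little value in shorter waits obtained at the expense of patient outcomes. The probability of that joint result is the one figure the section does not report.

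**Working it through.** **Inputs, all from the protocol article**
- "A total of 368 participants (184 per arm) will be recruited". With 15% loss, 184 × 0.85 = 156.4 evaluable per arm.
- PSFS: margin 0.7, SD 1.9, two-sided α 5% (lower limit of a 95% CI).
- Waiting time: difference 14 days, SD 43, two-sided α 5%, 15% loss.
- True PSFS difference: not stated. It is taken as 0, which reproduces the planned size: 155 evaluable per arm for 90% power, and 155/0.85 = 182.4, so 183 per arm against the planned 184.

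**Step 1. Reproduce the stated figures.** Normal approximation, power = Φ(δ / (SD × √(2/n)) − 1.96), with √(2/156.4) = 0.1131.
- PSFS: 0.7 / (1.9 × 0.1131) = 3.258; Φ(3.258 − 1.96) = 0.903. Stated: 90%.
- Waiting time: 14 / (43 × 0.1131) = 2.879; Φ(2.879 − 1.96) = 0.821. Stated: above 80%. A noncentral t calculation gives 0.819.

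Both stated figures reproduce, each as the power of a single test.

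**Step 2. Probability that both tests succeed.** Under independence, 0.903 × 0.821 = 0.741. For correlated test statistics (bivariate normal):

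| Correlation | Joint power | Waiting-time power given noninferiority shown |
|---|---|---|
| −0.5 | 0.726 | 0.804 |
| −0.3 | 0.730 | 0.809 |
| 0 | 0.741 | 0.821 |
| 0.3 | 0.757 | 0.839 |
| 0.5 | 0.771 | 0.854 |

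The last column is joint power divided by 0.903. Whatever the dependence, joint power lies between 0.903 + 0.821 − 1 = 0.724 and 0.821. It is 0.798 at a correlation of 0.8 and 0.804 at 0.85. At the lower bound the conditional power is 0.724/0.903 = 0.802, so a label of above 80% given noninferiority is safe on these inputs.

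**Step 3. Sensitivity to the other assumptions, under independence**
- No loss for waiting time (184 per arm): Φ(14 / (43 × √(2/184)) − 1.96) = Φ(3.123 − 1.96) = 0.878; joint 0.903 × 0.878 = 0.792.
- True PSFS difference of +0.1 in favour of the new service: first step 0.961, joint 0.789. Difference of −0.1: first step 0.797, joint 0.655.
- Baseline adjustment. The documents give no baseline correlation, so these values are assumed, and the PSFS SD is multiplied by √(1 − r²). With r = 0.3 the first step has 0.927, and the joint power is 0.761 with 15% waiting-time loss and 0.814 with none. With r = 0.5 the first step has 0.964, and the joint power is 0.792 and 0.846.

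**The case against.** The strongest reply is that nothing stated is wrong. The section lists its inputs, and they give 82.1%. Read in order, with the condition first and the power sentence after it, the figure can be taken as the power of the second step, and as such it holds. The protocol sets no target for joint power, so a joint figure below 80% breaks no commitment. All of this stands. A reader might infer an arithmetic error or an underpowered trial; the documents support neither.

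The reply also presses on how firm 74% is. Primary analysis plans a mixed model adjusted for baseline PSFS, site and subgroup, which may raise the power of the first step. Waiting time runs to the first appointment and does not rest on a follow-up survey, so 15% loss may be pessimistic. Either change lifts the joint figure, and the two together can take it past 80% (0.814 with an assumed baseline correlation of 0.3 and no waiting-time loss). This also stands, and it is why 74% should appear with its assumptions and a range. A reader should not take it as the trial's definite chance of success.

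The reply does not remove the point. The protocol does not label the figure as stand-alone or conditional, and the 15% loss for waiting time is its own assumption. Nor can the matter be left to the analysis plan, because the article itself states a power figure beside the hierarchy.

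**Conclusion.** The concern holds as a matter of labelling and completeness. The figure above 80% is the waiting-time test's own power (82.1%) and does not account for the hierarchical condition, which is met with about 90% probability. On the protocol's sample-size inputs, the probability of concluding both noninferiority and a waiting-time reduction is about 74% under independence, and 73% to 77% for correlations of −0.5 to 0.5. This rests on a true PSFS difference of 0, SDs of 1.9 and 43, 15% loss for both outcomes and no gain from covariate adjustment. With no loss for waiting time it is about 79%, and it is higher if baseline adjustment adds precision. It falls to about 65% if the new service is truly 0.1 points worse on the PSFS.

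**What to change.** In the Sample size section, say that the power above 80% applies to the waiting-time test given that noninferiority has been shown. Then add that the probability of concluding both is about 74% if the two tests are independent (73% to 77% for correlations of −0.5 to 0.5), assuming no true PSFS difference, 15% loss for both outcomes and no gain from adjustment, and about 79% with no loss for waiting time.

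The sample size, the margin, the outcome labels and the analysis do not change. The cost is a sentence or two and a less favourable figure on the page.
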